## Abstract

**Background:**

In rural Indigenous women, physical inactivity is a major modifiable risk factor for cardiometabolic illness and obesity. Thus, the objective was to describe the methodological design required to develop a randomized controlled trial to compare a culturally adapted cardiovascular dance intervention to traditional exercise on physical health, quality of life, and exercise-related psychosocial outcomes in rural Indigenous women with overweight/obesity as key determinants cardiometabolic conditions.

**Methods:**

Randomized, double-blind, parallel-group clinical trial. Twenty-two adults Mapuche women with overweight or obesity and cardiometabolic disorders from an Indigenous Community in Padre Las Casas, Chile, will be randomly allocated to a control group (*n* = 11) or a culturally adapted cardiovascular dance intervention group (*n* = 11). Two groups will receive one-hour supervision three times a week for 12 weeks. The primary goal is cardiorespiratory fitness, whereas secondary outcomes include physical health indices, health-related quality of life, motivation for physical activity, and perceived exercise barriers and advantages.

**Results:**

The culturally customized intervention is anticipated to yield increased levels of emotional well-being, perceived self-efficacy, and adherence in comparison to conventional exercise. The incorporation of Mapuche cultural elements, particularly traditional dancing, has the potential to enhance physical health, foster social engagement, reinforce cultural identity, and enhance community engagement.

**Conclusion:**

The objective of this trial is to evaluate the potential benefits and viability of culturally tailored physical activity interventions for Indigenous women. This will enhance the effectiveness of health promotion strategies that are context-specific and inclusive, as well as resolve a significant gap in the scientific literature.

**Clinical trials registration:**

Clinicaltrials.gov/study/NCT06903455, identifier NCT06903455

## Introduction

1

Physical inactivity is a well-established modifiable risk factor for obesity, cardiovascular disease, and related cardiometabolic conditions (1, 2). In Chile, obesity prevalence among women is among the highest in Latin America, a region disproportionately affected by the global obesity epidemic (3). National surveillance data indicate that the prevalence of excess malnutrition among women reaches 78.7%, according to the National Health Survey (ENS). Moreover, evidence indicates that Indigenous women exhibit higher rates of overweight and obesity than non-Indigenous women, particularly between 20 and 49 years of age (4). Likewise, women report significantly lower levels of moderate-to-vigorous physical activity compared with men (5). These disparities are further exacerbated among lower socioeconomic groups, who present higher levels of sedentary behavior and greater structural barriers to engaging in regular physical activity (6, 7).

In the Chilean context, Mapuche individuals face a distinct set of barriers to engaging in physical activity. Qualitative studies conducted with Mapuche adults and Indigenous health program workers have documented challenges such as discrimination within health services, limited cultural relevance of physical activity programs, and gaps between mainstream health initiatives and Indigenous worldviews. These issues, together with insufficient professional training to deliver culturally adapted exercise strategies, contribute to reduced participation in structured physical activity among Mapuche communities. Additionally, cultural and socioeconomic marginalization disproportionately affects Mapuche women, who often encounter systemic barriers and reduced access to opportunities for physical activity, reinforcing the need for interventions that acknowledge cultural identity and community context (8).

Obesity is frequently accompanied by stigma, with women experiencing a disproportionate burden of weight-related disadvantage in domains critical to personal well-being (9). Cultural factors can reduce engagement in physical activity. Evidence from Hispanic adolescents with type 2 diabetes and Latino adults with type 2 diabetes shows that culturally rooted barriers (and related distress) are linked to lower adherence to exercise recommendations (10). As countries progress economically, the burden of overweight increasingly shifts toward socioeconomically disadvantaged groups, with an inverse association between socioeconomic status and body mass index observed in women but not in men (11). In Chile, poverty remains more prevalent in rural areas (13.82%) than in urban settings (10.42%). Within the Araucanía region, 2 municipalities are predominantly rural or mixed, including Padre Las Casas, which is classified as mainly mixed (12). According to the 2017 Population Census, this municipality has 76,126 inhabitants, of whom 40.35% reside in rural areas and 48.2% identify as Indigenous (Mapuche) (13).

Regular physical activity is an effective long-term strategy for managing overweight and obesity, resulting in reduced cardiovascular disease risk and improved cardiorespiratory fitness (14). Cardiovascular dance (CD) is a popular physical activity among women, associated with increased intrinsic motivation, reduced body weight and fat mass, and metabolic enhancements in individuals with overweight, obesity, and type 2 diabetes (15). Exercise adherence is notably influenced by program characteristics such as enjoyment, supervision, social support, cultural relevance, and adaptability to daily routines, in addition to support from professionals and peers (16, 17).

From a psychosocial perspective, self-determination theory (SDT) offers a robust framework for understanding motivation for physical activity (18). SDT posits that sustained engagement is driven by satisfaction of the basic psychological needs for autonomy, competence, and relatedness (19). Culturally relevant interventions may foster autonomous motivation and reduce perceived barriers, particularly among women experiencing stigma, low self-efficacy, or cultural tensions related to exercise participation (20).

Cardiovascular dance modalities -i.e., dance-based, music-driven aerobic exercise- such as Zumba have demonstrated high adherence and beneficial effects on weight maintenance and cardiorespiratory fitness (21). “Fitfolk,” a culturally grounded CD discipline originating in northern Chile, integrates fitness exercises with Chilean and Latin American folk music and dance, aiming to promote physical and psycho-emotional well-being while strengthening cultural identity (22). However, no studies in Chile or Latin America have evaluated Fitfolk or similar culturally adapted CD interventions as strategies to address overweight, obesity, or cardiometabolic disease, particularly among Indigenous women. To date, no randomized controlled trials have examined such interventions in rural Mapuche communities.

The comparator for this trial will be a conventional physical exercise program, defined according to current clinical guidelines and standard care practices (23, 24), and aligned with recommendations from the European Association for the Study of Obesity (25). Both intervention and control groups will receive supervised exercise three times per week for 60 min over 12 weeks, ensuring equivalent exercise dose and professional contact time, thereby allowing isolation of the cultural component as the primary differentiating factor.

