## Research question

2

Is a culturally adapted cardiovascular dance program (Fitfolk) as effective as, or more effective than, a conventional physical exercise program in improving physical health, health-related quality of life, and exercise motivation, and in reducing perceived barriers to physical activity among rural Indigenous women with overweight or obesity and cardiometabolic risk in the commune of Padre Las Casas, Chile?

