##### Procedures

4.9.2.1

At the start of each session, participants’ blood pressure and heart rate will be measured to ensure safe participation in physical activity. Each session followed a standardized structure (Table 2). Although the intervention targets Mapuche women, traditional Mapuche ceremonial dances will not be incorporated due to their spiritual and ritual significance. Instead, Fit-Folk’s cultural adaptation is reflected in: (a) the use of folk and popular dance styles widely practiced in rural southern Chile, such as the cueca, rancheras, and cumbia, which are familiar and culturally significant to community members; and (b) the incorporation of deeply structured cultural elements, such as coordination with the Huichacura-Cayuqueo Indigenous Community, an all-female group format, culturally safe communication, and community-agreed norms. This approach ensures cultural relevance while maintaining respect for Mapuche ceremonial traditions.

**Table 2 tab2:** Structure of a Fit-Folk cardiovascular dance class.

Phase	Duration	Activity description	Intensity (Borg)	Dance styles	Country/folklore
Warm-up	8–10 min (2 to 3 songs)	Slow and progressive movements including joint mobility, basic dance steps, and dynamic stretching, aimed at increasing joint range of motion, body temperature, and cardiorespiratory activation.	Moderate, Borg 3–4	Huayno; Nicaraguan full-rhythm dances	CL and PE
Main development	35–40 min (14 to 16 songs)	The main phase of the session, characterized by higher-intensity rhythms and movements. Participants replicate Latin American folk choreographies guided by the instructor, emphasizing continuous movement and aerobic demand.	Moderate to Intense, Borg 5–9	Moderate-intensity dances: Tumbe; Afro-descendant Chilean rhythms from Arica; Colombian cumbia; Southern Chilean rancheras; Afrosaya (Bolivia); Chilean cueca. High-intensity dances: Tinkus; Forró (Brazil); Caporal; El Rin (Chile); Merengue.	BO, BR, CL, CO and PA
Cool-down/return to calm	8–10 min (2 to 3 songs)	Gradual reduction of movement intensity using slower dance steps, followed by static stretching to promote relaxation and recovery.	Low, Borg 1–3	Morenada; Venezuelan gaita; Peruvian waltz.	BO PE and VE

Borg, Borg rating of perceived exertion; BO, Bolivia; BR, Brazil; CL, Chile; CO, Colombia; PA, Panama; PE, Peru; VE, Venezuela.

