#### Title of the intervention and its justification

4.10.1

The control condition will consist of a group-based conventional physical exercise program combining resistance and cardiorespiratory training. This intervention was selected due to its documented effectiveness in improving anthropometric, metabolic, and cardiorespiratory outcomes (25, 41).

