#### Procedures

4.10.3

Each session will be organized into structured blocks. The initial warm-up block included dynamic stretching (42), joint mobility exercises, movement-specific preparatory drills (43), and neuromuscular activation.

The primary training block will emphasize high neuromuscular demand exercises (e.g., squats, deadlifts, overhead presses, rows), with exercise selection based on planned movement patterns and load prescription tailored to training objectives. Resistance training intensity will be monitored using the OMNI-RES perceived exertion scale (44).

Next, a secondary resistance block will be performed, characterized by reduced intensity and volume. An auxiliary block will be then implemented, focusing on core strengthening (45), joint mobility, large-joint stability, and advanced technical movements.

The metabolic conditioning block incorporated interval-based methods targeting both cardiorespiratory and muscular systems, monitored using the speech test (46) and Borg scale (47), including high-intensity interval training (HIIT) protocols when appropriate (48). Sessions concluded with a cool-down phase consisting of breathing exercises, joint mobilization, and static stretching (49, 50).

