#### Training structure and frequency

4.10.6

A full-body training approach (51) using mixed training methods (52) will be employed. The 12-week program will be divided into three mesocycles: anatomical adaptation/general strength (weeks 1–4), hypertrophy/general strength (weeks 5–8), and muscular endurance/general strength (weeks 9–12). Exercise selection and distribution will be based on fundamental movement patterns and upper- and lower-limb push–pull dynamics (53). Training frequency and session duration matched the experimental group (three sessions per week, ~60 min each) (54).

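### Equal session schedules do not equalise exercise dose, so the trial cannot isolate the cultural component from exercise modality

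*Protocol article*

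**What the plan says.** The Introduction of the protocol article justifies the comparator by its schedule. Both arms exercise under supervision three times a week, 60 minutes a time, for 12 weeks, "ensuring equivalent exercise dose and professional contact time, thereby allowing isolation of the cultural component as the primary differentiating factor". That sentence takes two steps: from an equal schedule to an equal dose, and from an equal dose to isolation of culture.

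The methods sections claim less. Section 4.10.6 says only this: "Training frequency and session duration matched the experimental group". They also describe two different kinds of exercise:

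- **Fit-Folk** (sections 4.9.2 to 4.9.2.4, Table 2): aerobic dance whose main phase lasts "35–40 min (14 to 16 songs" per session, without added resistance equipment.
- **Comparator** (sections 4.10.1 to 4.10.6): a "group-based conventional physical exercise program combining resistance and cardiorespiratory training". Its primary block consists of lifts such as squats and deadlifts. Then "a secondary resistance block will be performed, characterized by reduced intensity and volume", followed by core and mobility work. The aerobic element comes after that: "The metabolic conditioning block incorporated interval-based methods targeting both cardiorespiratory and muscular systems". On periodisation the text begins: "The 12-week program will be divided into three mesocycles: anatomical adaptation/general strength". The later mesocycles pair general strength with hypertrophy and with muscular endurance.

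Section 4.14.1 makes cardiorespiratory fitness, estimated by a step test, the primary outcome. Section 2 asks a whole-programme question: whether Fit-Folk is "as effective as, or more effective than, a conventional physical exercise program".

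**The concern.** To isolate culture, the arms would have to be alike in everything else that could move the outcome. Here the type of exercise differs as well, and it differs on the axis that the primary outcome measures. The article itself credits the dance modality with such effects. Section 4.9.1 justifies the intervention by evidence that cardiovascular dance raises VO₂max and improves quality of life, and the Introduction cites Zumba for gains in cardiorespiratory fitness and adherence. On that account dance could change the primary outcome with no cultural adaptation at all.

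What is at stake is attribution. A difference between arms could come from modality, from culture or from both. A null result could hide effects in opposite directions. The Discussion carries the same logic forward. It suggests, in hedged terms and beside an alternative, that null metabolic results might mean training volume and intensity matter more than cultural adaptation. This contrast cannot separate those explanations. The Discussion also hopes the findings will inform intercultural health policy, where a wrong attribution to culture would matter.

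**Working it through.** **1. What is matched.** Sessions per arm: 12 weeks × 3 = 36. Contact time: 36 × 60 min ÷ 60 = 36 h per arm. Group size and venue (4.9.2.3, 4.10.5) and the session safety rules (4.9.2.5) are also common to both arms. The contact-time half of the Introduction's statement therefore stands.

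**2. What is not matched.**

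| Feature | Fit-Folk | Comparator |
|---|---|---|
| Main content | Continuous aerobic dance (Table 2) | Two resistance blocks, core/mobility block, one interval block (4.10.3) |
| Resistance equipment | None added (4.9.2) | Kettlebells, dumbbells, bands, suspension trainers, medicine balls (4.10.2) |
| Intensity | Modified Borg 3–4 in weeks 1–3, then 5–9 (4.9.2.4) | OMNI-RES for resistance; speech test and Borg for conditioning; no target value given (4.10.3) |
| 12-week progression | Tempo, choreography, movement intensity (4.9.2.4) | Adaptation, hypertrophy and muscular endurance, each paired with general strength (4.10.6) |
| Provider | Certified Fit-Folk instructor with rural community experience (4.9.2.2) | Physical education professional (4.10.4) |

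**3. Size of the dance arm's aerobic phase.**

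- Lower end: 36 × 35 ÷ 60 = 21.0 h; 21 ÷ 36 = 58%.
- Upper end: 36 × 40 ÷ 60 = 24.0 h; 24 ÷ 36 = 67%.
- Weeks 1–3: 3 × 3 = 9 sessions, 9 ÷ 36 = 25%, intermittent and at Borg 3–4. Without them the total is 27 × 35 ÷ 60 = 15.75 h to 27 × 40 ÷ 60 = 18 h.

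**4. Could the comparator's aerobic minutes be equal?** The article does not give its block durations, so no ratio can be stated. A break-even needs only stated figures. In a session from week 4 on, the conditioning block would have to last 35–40 minutes. That leaves 60 − 40 = 20 to 60 − 35 = 25 minutes for five other parts: warm-up, primary resistance, secondary resistance, core/mobility and cool-down. The average would be 20 ÷ 5 = 4 to 25 ÷ 5 = 5 minutes each. This counts minutes and not intensity, and treats only the conditioning block as aerobic.

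**5. Is culture itself cleanly contrasted?** Section 4.9.2.1 lists the all-female group among Fit-Folk's cultural adaptations. Table 1 admits only women of this one community to the trial, so the comparator groups appear to be all-female too. This is a supporting point and does not carry the conclusion.

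**The case against.** The strongest reply is that this is one sentence of rationale on which nothing depends. The abstract, research question and objective all compare whole programmes, and the group × time analysis in section 4.16 tests that contrast. No sample-size input or decision rule uses isolation of culture. The sentence also calls culture the primary, not the only, differentiating factor. All of this is true. It limits the consequence, but it does not make the statement correct: nothing shows that culture outweighs modality, and neither the assurance of equal dose nor the word isolation is hedged.

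A second reply is that comparator minutes are detail a condensed article may leave to the full protocol, and that the comparator includes cardiorespiratory work, possibly high-intensity intervals. Agility ladders and cones might add aerobic work elsewhere in the session. This stands against any claim that the aerobic dose is unequal, and none is made here; nor is a direction of bias asserted. It does not rescue isolation. Even with equal aerobic minutes, resistance training against dance would remain a second difference between the arms.

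Third, the hour and percentage figures are nominal. Table 2 phases sum to 51–60 minutes, sessions are described as approximate, and the early low-intensity sessions sit inside the 21–24 hours. That is fair; the figures show scale only. The provider difference is also a lesser point, since a Fit-Folk instructor is arguably part of the cultural package and the comparator's professional is not said to lack community experience.

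**Conclusion.** The concern holds. The Introduction claims a property the design does not have. Equal frequency, session length and contact time (36 sessions, 36 h per arm) are secured. Equal exercise dose is not shown, and culture is not isolated, because modality changes with it. This conclusion rests on the described content of the two programmes and needs no assumption about the comparator's block minutes. Equal aerobic minutes are not excluded, but would squeeze five session parts into 20–25 minutes if the conditioning block were the only aerobic work.

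The randomised comparison of the two programmes, which is what section 2 asks for, is unaffected. What fails is attribution of any result, positive or null, to the cultural component.

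**What to change.** 1. In the Introduction, claim only what is matched, for example: *ensuring equal session frequency, duration and professional contact time*.
2. Delete the clause about isolating the cultural component.
3. Word conclusions as a culturally adapted dance programme against a mixed resistance-and-interval programme, in line with section 2. In the Discussion, remove or qualify the suggestion that null metabolic results could separate training volume and intensity from cultural adaptation.
4. Optionally, report planned minutes per block for each arm from the session plans, labelled as planned.

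Items 1 to 3 are wording only. Item 4 should need no more than reading the session plans. Programmes, randomisation, endpoint and analysis stay as they are. The price is a narrower claim: the trial could no longer say that culture itself caused a result.

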##### Intervention fidelity

4.9.2.7

Session fidelity will be assessed using post-session satisfaction surveys. Additionally, digital questionnaires will be administered throughout the intervention to capture covariates related to behavioral changes and barriers associated with participation in Fit-Folk Cardiovascular Dance activities.

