#### Provider

4.10.4

Sessions will be delivered in person by a qualified physical education professional with experience in adult fitness training.

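### Equal session time does not make the exercise dose equivalent or isolate the cultural component: modality, instructor and class differ by arm and intensity is not matched

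*Protocol article*

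**What the plan says.** The last paragraph of the Introduction describes the comparator. It states that frequency, session length and programme length are the same in both arms, "ensuring equivalent exercise dose and professional contact time", and concludes that this works by "thereby allowing isolation of the cultural component as the primary differentiating factor".

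The two programmes are then described separately. Section 4.9.2.1 (Table 2) gives Fit-Folk a main phase of 35 to 40 minutes of folk choreography, "emphasizing continuous movement and aerobic demand". Section 4.10.1 defines the comparator as a "group-based conventional physical exercise program combining resistance and cardiorespiratory training", and section 4.10.4 assigns it to a "qualified physical education professional with experience in adult fitness training". Section 4.14.1 makes cardiorespiratory fitness, estimated from a step test, the primary outcome.

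On delivery, section 4.9.2.7 says: "Session fidelity will be assessed using post-session satisfaction surveys". The Discussion suggests in advance that a lack of metabolic effect may mean training volume and intensity matter more than cultural adaptation alone.

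**The concern.** Isolating one component requires arms that are alike in everything else that could move the outcome. Here the arms differ in the kind of exercise performed, and the primary outcome measures the response to exercise. If Fit-Folk does better on estimated VO₂max, the Introduction would have readers credit culture, when the aerobic content, the instructor or the class could explain the result equally well. If there is no difference, the Discussion's suggested reading sets volume and intensity against culture, although the design does not separate them. The trial is meant to inform intercultural health policy, so what the result is attributed to matters as much as the result.

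**Working it through.** **What is equal.** 3 sessions × 12 weeks = 36 sessions; 36 × 60 min = 2,160 min = 36 h per arm. The contact-time part of the claim is confirmed. Supervision, class size and venue also match (4.9.2.3, 4.10.5).

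**What is not equal.**

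| Feature | Fit-Folk | Conventional exercise |
|---|---|---|
| Modality | Aerobic dance, no resistance equipment (4.9.2, 4.9.2.1) | Primary and secondary resistance blocks, an auxiliary core and mobility block, one interval conditioning block; kettlebells, dumbbells, bands (4.10.2, 4.10.3) |
| Emphasis over 12 weeks | Intermittent practice in weeks 1–3, then progressively more demanding dance (4.9.2.4) | Three cycles, each with a general-strength label (4.10.6) |
| Intensity | Modified Borg 3–4 in weeks 1–3, rising to 5–9 (4.9.2.4) | OMNI-RES for resistance; speech test and Borg for conditioning, HIIT where suitable; no target stated (4.10.3) |
| Instructor | Certified Fit-Folk instructor with local community experience (4.9.2.2) | Physical education professional (4.10.4) |
| Class | 11 participants, the whole arm (4.9.2.3) | 11 participants, the whole arm (4.10.5) |

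**What the analysis can identify.** Section 4.16 fits group, time and group × time. With two arms and two time points, the interaction is a single number, the difference between arms in mean change. Written additively for illustration:

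Δ = culture + modality + intensity + instructor + class

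That is one estimate for five components. Each component takes one value in each arm, so no term in the model can separate them.

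- Δ > 0 is compatible with a culture component of zero.
- Δ = 0 is compatible with a culture component of either sign, offset by the others.

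**The other side of the contrast.** Section 4.9.2.1 counts an all-female format and coordination with the community among the cultural elements. Both arms enrol only women of this one community (Table 1) and train at the same community centre. Some of the component said to be isolated is therefore likely to be present in both arms.

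**Whether dose could be checked afterwards.** Satisfaction surveys do not measure dose. Section 4.7 says instructors monitor physiological responses during sessions, and section 4.10.3 names exertion scales for the comparator. Relevant observations are thus made, but the article does not plan to report them by arm.

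**The case against.** The strongest defence is that the sentence is background rationale, says primary rather than sole, and does not drive the analysis. The research question (section 2) and objective (section 3) compare one programme with another, and the group × time model estimates exactly that. Section 4.10.6 claims a match only on frequency and session length. The Discussion is hedged, concerns metabolic outcomes rather than VO₂max, and offers a second explanation (longer programmes and more community engagement). All of this stands, and it limits the point to wording and interpretation. It does not rescue the sentence, because a difference in exercise type is not secondary when the outcome is fitness. The limitations listed in the Discussion do not mention the confounding.

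A reader might infer more than the document supports:

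- **A several-fold difference in aerobic dose.** The article gives no length for the comparator's conditioning block, so any ratio would rest on an invented figure. Counting all 36 dance main phases as hard aerobic work is also wrong. Weeks 1–3 cover 9 sessions at Borg 3–4, leaving at most 27 × 35–40 min = 15.75–18 h at Borg 5–9. Minutes of dance and minutes of intervals are not interchangeable either.
- **That Fit-Folk is the harder programme.** The comparator may include HIIT. The text shows that intensity is not matched, not which arm is higher.
- **An inflated type I error from one class per arm.** This would apply if the target were a programme effect beyond these two classes, and the document gives no intraclass correlation. If the contrast is defined as each programme with its instructor and class, class effects belong to what is estimated.
- **That intensity goes unmeasured.** Sections 4.7 and 4.10.3 describe monitoring.
- **That the abstract contradicts the intervention.** It speaks of "The incorporation of Mapuche cultural elements, particularly traditional dancing", while section 4.9.2.1 says "traditional Mapuche ceremonial dances will not be incorporated due to their spiritual and ritual significance" and uses folk and popular styles familiar to the community. This is loose wording and a minor side point.

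**Conclusion.** The isolation and equivalent-dose statements are wrong as written and should be corrected. Scheduled contact time is equal at 36 h per arm. Modality, instructor and class are fully confounded with the cultural component, and intensity is not matched, in an unknown direction. Neither a positive nor a null result can be attributed to cultural adaptation. The randomised comparison of the two whole programmes is unaffected and answers the stated research question.

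The conclusion depends on no assumed number. It rests on the article's own arm descriptions and on reading 11 participants per group, in arms of 11, as one class per arm. Block lengths or targets in a fuller protocol could show how far the doses differ. They would not separate exercise type, instructor or class from culture.

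**What to change.** 1. **Introduction, comparator paragraph.** Replace the equivalent-dose claim with equal scheduled contact time. Replace the isolation claim with a statement that the trial compares two whole programmes, each with its own exercise content, instructor and class.
2. **Discussion.** List modality, intensity, instructor and class as limits on attribution. Drop the reading of a null result as volume and intensity against culture.
3. **Delivery data.** As a cheap addition, record in both arms the session exertion ratings and physiological responses that instructors monitor, and report them by arm. Satisfaction surveys can stay as a measure of satisfaction but should not stand as evidence of dose.
4. **Abstract (minor).** Align the phrase on traditional dancing with section 4.9.2.1.

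Nothing changes in design, sample size, treatment or primary analysis. The cost is a few sentences, a small logging burden (the article fixes heart rate only at session start, so some recording may be new) and a narrower conclusion. Isolating culture itself would need a different comparator, namely the same kind of dance exercise without the cultural content. That would be another trial and is not asked for here.
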